## Abstract

Background: Age-related changes negatively affect physical fitness, body composition, and executive function and produce a decrease in regucalcin level expression in blood. The square-stepping exercise (SSE) is a balance and lower-limb strength training programme used to prevent falls and stimulate cognitive function in older adults. This project aims to analyse the effects of SSE on executive function, regucalcin expression, fall prevention, body composition, and physical fitness in people over 65 years old. Methods: A randomized controlled trial will be conducted. A total of 90 older people over 65 years old will be recruited and randomly assigned to 2 groups: experimental (*n* = 45) and control (*n* = 45). The experimental group will perform an SSE-based intervention for 6 months (2 times per week), while the control group do not follow any treatment. Results: The main outcome will be balance, but other motor (body mass index, upper- and lower-limb strength, flexibility, and speed-agility) and cognitive variables (executive functions and attention) will be assessed. The expression of regucalcin levels will also be evaluated. Therefore, this project aims to analyse the effect of a 6-month SSE intervention on cognitive and motor competence, physical fitness, regucalcin levels, fall risk, and body composition in older people. If the intervention proves to be effective, it could be implemented in centres, entities, and associations specialized in elderly care.

## 1. Introduction

Ageing is associated with some body changes [1] such as decreases in muscle mass, bone mass, and cognitive function and increases in fat mass and blood pressure [2,3], which leads to worse functional health and, consequently, poorer quality of life. These changes can be aggravated by high rates of sedentary lifestyles, negatively affecting physical fitness, body composition, and executive function [4]. Thus, it is important to maintain the autonomy and independence of older people through “active” ageing, a term used by the World Health Organization (WHO, Geneva, Switzerland) that establishes physical exercise as an effective therapy to minimize and prevent the negative effects of ageing.

In order to know the negative effects of ageing, regucalcin has appeared as a calcium-binding protein discovered in 1978 [5] that has antitumor activity [6], is sub-expressed in cancerous tissues [7,8], and prevents apoptosis [9]. Although it presents numerous functions, its use as a biomarker that decreases with ageing in animals [7] and humans [10] is the special interest for the present project. Despite this, there is only one study [11] which analysed the effects of whole-body vibration physical exercise on regucalcin levels in humans, showing an increase in it.

As with regucalcin, ageing and a sedentary lifestyle also affects executive function. The study of executive function in humans has been approached using near-infrared haemoencephalography (nir-HEG). It is a novel technique that estimates brain activation in the frontal lobe from the amount of haemoglobin oxygenation in blood flow of this area [12]. To date, the few existing studies that use nir-HEG have been applied to children with mental problems or obesity and healthy people [13]. However, there is no available data related to executive function and falls in older people. Thus, the study of executive functioning could play an important role in the prevention of falls and performing motor activities and cognitive tasks simultaneously (known as Dual Task—DT) in older people [14].

Many of the tasks of daily life involve DTs, which are a matter of concern given that because of ageing, older people have problems performing the daily live activities simultaneously. The ability to perform any task may be impaired due to limited attentional resources [15], increased risk of falls [16], loss of independence, and impaired quality of life. Previous studies analysing the effect of DT in older women with fibromyalgia found that gait pattern is affected when an additional cognitive task is added to the primary motor activity; so the walking pattern may be safer and more stable if attention is focused on two simultaneous tasks [17,18]. However, no studies have investigated the impact of DT-based exercise programs on cognitive activity and executive function.

Square stepping exercise (SSE) is a type of physical exercise used in the elderly to reduce the risk of falls [19], but its effects on executive function and regucalcin levels have not been examined. Therefore, this study will analyse the effects of SSE on regucalcin, executive function, physical fitness, balance, fall risk, fear of falling, and body composition in older people. In addition, it will assess the relationship between changes in executive function and regucalcin, physical fitness, balance, fall risk, fear of falling, and body composition in older people.

We hypothesized that (1) SSE will enhance regucalcin levels, executive function, physical fitness, balance, fall risk, fear of falling, and body composition in older people, and (2) changes in executive function and regucalcin will be related to falls, body composition, and physical fitness in older people.

## 2. Material and Methods

### 2.1. Study Design

A randomized controlled trial with an assignment ratio of 1 to 1 to experimental and control groups will be conducted. The methodology followed will be the Consolidated Standards of Reporting Trials Statement (CONSORT) methodology [20].

### 2.2. Ethical Approval

The current protocol has been approved by the Bioethics and Biosafety Committee at the University of Extremadura (approval number: 109/2021) according to the Helsinki Declaration. Indeed, it has been registered in the Clinical Trials Registry provided by the Australian New Zealand Clinical Trial Registry (Request number: 383217; https://www.anzctr.org.au/, accessed on 29 November 2021).

### 2.3. Sample Size Calculation

The number of participants to be included in the studies has been calculated based on the change in plasma regucalcin levels, this actual minimum difference being 38.48 AU [21] with a power of 0.65. Hence, a total of 90 participants are required for the studies to be conducted (45 in the experimental group and 45 in the control group), accepting an alpha risk of 0.05. The common standard deviation in regucalcin is assumed to be 192.4 [11] and a loss-to-follow-up rate of 20% has been estimated.

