#### 2.7.1. Primary Outcomes

-**Balance**. One leg-stance and four square steps test will be used to asses static and dynamic balance, respectively.
○*One leg stance*. The test consists of standing on one leg for as long as possible (during a maximum lapse of 45 s) while keeping the arms crossed at all times. The test starts when the foot is lifted off the ground and ends when: (1) the arms are uncrossed, (2) the lifted foot touches the ground, (3) when more than 45 s have elapsed. Two variants of this test will be performed, with eyes open (ICC = 0.99) and with eyes closed (ICC = 0.95) [26,27]. Three repetitions of the test shall be performed, and the best time achieved will be recorded.○*Four square steps test (FSST)*. Four squares are formed by placing tape on the floor. At the start of the test, participants standing in the first square in front of square number 2 are asked to walk consecutively (1-2-3-4-4-4-3-2-1) without touching the holes and with both feet in contact with the ground. The time required to complete the full cycle will be recorded (ICC = 0.98) [28].-**Applicability**. All the older people who can undertake the suggested training. If any participant is not capable to perform the intervention, the reason should be mentioned.-**Safety**. In the event of any incident, damage, or trouble during the sessions, a record shall be kept and the source of the incident, injury, or problem noted.

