#### 2.7.2. Secondary Outcomes

**Sociodemographic data**. Attendees will be questioned about their age, revenue, education level, and marital status.

**Height**. It will be assessed using a stadiometer (SECA 225, SECA, Hamburg, Germany). Subjects will stand with feet together, heels, buttocks, and upper back in contact with the scale and head in Frankfort’s plane.

**Bodyweight, fat mass and muscle mass**. Bodyweight shall be measured with a body composition analyser (TANITA MC-780 MA, Tanita Corp., Tokyo, Japan). Estimation of fat and muscle mass will be obtained by electrical bio-impedance using regression formulas.

**Executive function**. As part of the measurement of balance-related tests, subjects will be tested in DT using the nir-HEG headband to observe brain activation. The X-Wiz model will be used for cortical activation measurements in the Fp1 and Fpz/Cz regions of the Nir-HEG/Quantified-EEG/HRV system. The measurements will be based on the multimodal headband and pendant system developed to simultaneously combine the monitoring of Hemoencephalography in the frontal lobe (HEG), 2-channel Electroencephalography (EEG) by theta/Beta ratio, and heart rate (HRV) by the finger sensor [29].

**Regucalcin**. Blood samples will be obtained from the participants by fasting venous puncture in the antecubital vein (10 mL). It will use sterile material by qualified personnel, and these will be evaluated by Western blotting technique. The protocol has been described previously [11].

**Physical fitness**. They will be assessed with the following tests of the Senior Fitness Test Battery [30].

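### N = 90 is justified only by regucalcin, a secondary outcome; balance, the main outcome, has no target difference, SD or power, and the regucalcin calculation cannot stand in for it

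*Protocol article*

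**What the plan says.** The Abstract is direct about what decides the trial: "The main outcome will be balance". Section 2.7.1 (Primary Outcomes) lists balance first, alongside applicability and safety, and explains: "One leg-stance and four square steps test will be used to asses static and dynamic balance, respectively". One-leg stance is itself two measures: "Two variants of this test will be performed, with eyes open (ICC = 0.99) and with eyes closed (ICC = 0.95"). With the four square steps test (FSST) that makes three timed balance measures. None is singled out, and section 2.7 schedules them at baseline and months 2, 4 and 6 without naming a primary visit. The only statistics attached to them are reliability coefficients.

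Regucalcin appears in section 2.7.2 under the heading Secondary Outcomes, as a blood marker measured by Western blot.

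Section 2.3 nevertheless says: "The number of participants to be included in the studies has been calculated based on the change in plasma regucalcin levels", with "this actual minimum difference being 38.48 AU [21] with a power of 0.65". It adds a common SD of 192.4, an alpha of 0.05 (sidedness not given) and 20% loss to follow-up, and arrives at 45 per arm. It offers no other basis for N and no reason for sizing on this marker.

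**The concern.** A sample size statement should tell the reader what the trial can detect on the outcome that decides it. Here the only such statement belongs to another outcome. Sizing on a secondary outcome can be defended if that outcome is the more demanding one, so that the primary is covered with room to spare. The article does not argue this, and the argument would work only if the regucalcin calculation itself held.

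At stake is how the balance result will be read. Without a target difference on a named balance measure, there is no prespecified yardstick for deciding whether a neutral result rules out a worthwhile effect, or whether a positive one is as large as the trial was built to find.

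**Working it through.** **Inputs.** From section 2.3: difference 38.48 AU, SD 192.4, alpha 0.05, power 0.65, loss 20%, 45 per arm. Evaluable after loss: 45 × 0.80 = 36 per arm. From section 2.7.1: no difference, SD or power for any balance measure. Assumed here: a two-sided test (one-sided shown as a check), and baseline to follow-up correlations of 0.5 and 0.7 for balance.

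**Step 1: reproduce the plan's figure.** Standardised difference = 38.48/192.4 = 0.20.

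Per-arm size for two means = 2(z_alpha + z_power)²/d² = 2 × (1.960 + 0.3853)²/0.20² = 275.02, so 276 per arm (552 in total). Allowing for loss, 276/0.80 = 345 per arm (690). One-sided, the figures are 207 per arm, or 259 after loss. The stated 45 per arm is not reproduced.

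Power on the stated inputs = Φ(d√(n/2) − 1.960):

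| Per arm | d√(n/2) | Two-sided power | One-sided power |
|---|---|---|---|
| 45 | 0.949 | 15.6% | 24.3% |
| 36 | 0.849 | 13.3% | 21.3% |

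**Step 2: other routes to 90.**
- A one-sample formula at 65% power gives 138 (two-sided) or 104 (one-sided) before loss.
- If 192.4 is a cross-sectional SD and the analysis is of change or is baseline-adjusted, 65% power two-sided needs an effective SD of about 78 AU (45 per arm) or 70 AU (36 per arm). That implies a correlation of about 0.91 to 0.94, which the article does not state.
- Repeated-measures ANOVA with four visits, f = 0.10 (0.20 SD) and an assumed correlation of 0.5 gives, at N = 90, 59.6% for group × time and 22.1% for the group effect. At N = 72 these fall to 49.2% and 18.5%.
- Entering 0.20 as Cohen's f for the group effect gives 66.0% at N = 90. But f = 0.20 is 0.40 SD, twice the stated difference, and at N = 72 the power is 56.2%.

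None of these reproduces 90 from the stated inputs with the stated loss.

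**Step 3: what 90 can detect on balance.** No N for balance can be computed, because the article gives neither a difference nor an SD. The reverse question can be answered in SD units. Smallest difference detectable with 80% power, two-sided 0.05, from the noncentral t distribution; baseline adjustment multiplies it by √(1 − r²), which is 0.866 for r = 0.5 and 0.714 for r = 0.7:

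| Evaluable per arm | Unadjusted | r = 0.5 | r = 0.7 |
|---|---|---|---|
| 45 | 0.597 SD | 0.517 SD | 0.426 SD |
| 36 | 0.670 SD | 0.580 SD | 0.478 SD |

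**The case against.** Sizing on a secondary outcome is not a logical error, and the Introduction lists regucalcin first among the effects to be studied and in the first hypothesis, so the choice may be deliberate. That stands as far as it goes: a reader might infer that the sections contradict each other, but strictly the choice is unexplained rather than impossible. It does not supply a power statement for balance.

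A reader might also infer that 0.65 will be mistaken for the power on balance. The wording does not support this, since section 2.3 ties the figure to regucalcin.

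Nor will a neutral balance result be uninterpretable. Section 2.8 plans Cohen's d with a 95% confidence interval, and an interval shows which effects are excluded whatever power was planned. What is missing is the difference to judge it against.

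It is also tempting to compare the 0.48 to 0.67 SD detectable on balance with the 0.20 SD used for regucalcin. That comparison is not valid: the outcomes differ, the power levels differ (80% against 65%), and SD units of a blood marker and a timed test share no clinical scale.

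Finally, the detectable differences above model one baseline-adjusted follow-up visit, while section 2.8 plans repeated-measures ANOVA over four visits. This is a fair limit on the exact values. It does not touch the main point.

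**Conclusion.** The point holds: N = 90 rests solely on a secondary outcome, no reason is given, and the main outcome has no target difference, SD or power. The regucalcin calculation cannot fill the gap, because on its own inputs it delivers about 16% power with 45 per arm and 13% with 36 per arm (two-sided), not 65%. The one-sided figures of 24% and 21% do not rescue it. This rests on reading 192.4 as the SD that applies to the comparison; only an unstated correlation of about 0.91 to 0.94 would bring the power to 65%.

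A reader might go further and conclude that 90 is too few for balance. The article does not support that. If the true effect on the chosen measure is around 0.6 to 0.7 SD, or around 0.5 SD with a strong baseline correlation, 90 would be adequate. Whether such an effect is plausible or worthwhile cannot be judged from the article. This is also not a case of detail left to a fuller document: the article presents a sample size calculation, and attaches it to an outcome that does not decide the trial.

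**What to change.** 1. In section 2.7.1, name one balance measure (one-leg stance eyes open, one-leg stance eyes closed, or FSST) and one time point as primary.
2. Rewrite section 2.3 as what the fixed N of 90 can detect on that measure: about 0.67 SD at 80% power with 36 evaluable per arm unadjusted, or 0.58 to 0.48 SD for a baseline correlation of 0.5 to 0.7, with the correlation labelled as assumed. Convert this to seconds with an SD from a justified source. The balance references appear beside reliability coefficients only, so whether they contain a usable SD has to be checked. Say whether a difference of that size is plausible and worth detecting.
3. Describe regucalcin in section 2.3 as secondary, and replace its power of 0.65 with the value the inputs support (about 16% with 45 per arm, 13% with 36, two-sided). If other inputs were used, such as the SD of the change, state them so that the figure can be reproduced.

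Making regucalcin primary instead would also align the sections, but it is not a free alternative: on the stated inputs 65% power needs 552 participants, or 690 after 20% loss.

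The cost of steps 1 to 3 is recalculation and rewording in two sections, plus finding one SD. No participants are added. The downside is that the stated figures become less favourable than those now in the article.

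### The stated power of 0.65 does not follow from the protocol's own inputs: 38.48 AU, SD 192.4 and 45 per arm give about 15% (13% after 20% loss)

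*Protocol article*

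**What the plan says.** Section 2.3 (Sample Size Calculation) says that the number of participants was "calculated based on the change in plasma regucalcin levels". The inputs are:

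- **Difference and power:** "this actual minimum difference being 38.48 AU [21] with a power of 0.65".
- **Variability and loss:** "The common standard deviation in regucalcin is assumed to be 192.4 [11] and a loss-to-follow-up rate of 20% has been estimated".
- **Significance level:** "accepting an alpha risk of 0.05", with no statement of one- or two-sided testing.
- **Conclusion:** 90 participants are needed, 45 per arm.

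No within-person correlation is given. It is also not said whether the 90 already allows for the 20% loss, or whether 192.4 is the SD of regucalcin levels or of their change. Section 2.8 (Statistics) plans a repeated measures ANOVA adjusted for age and baseline, testing time and group × time. Section 2.7 sets assessments at baseline and months 2, 4 and 6.

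**The concern.** The section prints every input of a two-group comparison of means, so the power can be recomputed. The difference is one fifth of a standard deviation, and 45 per arm is far too few to detect that with 65% power.

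This is the only reasoning offered for N = 90, and the first hypothesis in the Introduction includes a rise in regucalcin. A reader told that power is 0.65 would treat a null result as moderate evidence against a 38.48 AU effect. At about 15% power it is close to uninformative on that question.

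The opposite error is also likely. In an unadjusted comparison with 45 per arm, an observed difference must exceed 1.987 × 192.4 × √(2/45) = 80.6 AU to be significant. That is more than twice the stated minimum difference, so if the true effect is near 38.48 AU, any significant estimate in the right direction will overstate it at least twofold.

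**Working it through.** **Inputs (section 2.3).** Difference 38.48 AU; SD 192.4; alpha 0.05 (two-sided assumed, one-sided also tried); 45 per arm; 20% loss, giving 45 × 0.8 = 36 per arm; stated power 0.65.

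**Standardised difference.** d = 38.48 / 192.4 = 0.20.

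**1. Attempt to reproduce 0.65.** Two-sample t test, noncentral t with 2n − 2 degrees of freedom and noncentrality d√(n/2).

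| n per arm | Noncentrality | Two-sided power | One-sided power |
|---|---|---|---|
| 45 | 0.20 × √22.5 = 0.949 | 15.5% | 24.1% |
| 36 | 0.20 × √18 = 0.849 | 13.3% | 21.1% |

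The stated 0.65 is not reproduced.

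**2. Sample size that would give 0.65.** n per arm = 2(z₀.₉₇₅ + z₀.₆₅)²/d² = 2(1.960 + 0.385)²/0.04 = 275.02, rounded up to 276. That is 552 evaluable. With 20% loss, 276/0.8 = 345 per arm, or 690. A one-sided test needs 207 per arm before loss.

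**3. Other readings of the same inputs.**

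- A one-sample or paired formula needs 138 (two-sided) or 104 (one-sided) before loss, and gives at most 37% power with 45.
- Reading 0.65 as the type II error (power 0.35) needs 124 (two-sided) or 80 (one-sided) per arm.

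None gives 0.65 or N = 90.

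**4. Difference the planned size can detect (two-sided, noncentral t).**

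| n per arm | 65% power | 80% power |
|---|---|---|
| 45 | 0.500 SD = 96 AU | 0.597 SD = 115 AU |
| 36 | 0.560 SD = 108 AU | 0.670 SD = 129 AU |

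**5. Baseline adjustment, if 192.4 is an SD of levels.** Let r be the correlation between visits; its values here are assumptions, since the protocol gives none.

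- *One adjusted visit.* The effective difference is 0.20/√(1 − r²). At r = 0.5, power is 19% (45 per arm) or 16% (36). At r = 0.8 it is 35% or 29%. Reaching 65% needs √(1 − r²) = 0.20/0.500 or 0.20/0.560, so r = 0.916 or 0.934.
- *Change score.* The effective difference is 0.20/√(2(1 − r)). Reaching 65% needs r = 0.920 or 0.936.
- *Mean of the three later visits, adjusted for baseline, equal correlations.* The effective difference is 0.20/√((1 + 2r)/3 − r²). At r = 0.8 this is 0.20/√0.2267 = 0.42, with power 50% (45 per arm) or 42% (36). Reaching 65% needs r = 0.867 or 0.896.

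**6. The planned group × time test over four visits.** A 0.20 SD difference corresponds to f = 0.043 if present in full from month 2, or f = 0.037 if it grows linearly to month 6. With noncentrality N × 4 × f²/(1 − r):

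| r | N = 90 | N = 72 |
|---|---|---|
| 0.5 | 14% / 11% | 12% / 10% |
| 0.8 | 30% / 23% | 25% / 19% |

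(Each cell: full effect from month 2 / linear growth.)

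**The case against.** The best defence is that section 2.8 plans a baseline-adjusted, repeated-measures analysis, so an unadjusted t test is the least favourable reading. The document sizes on change but gives an SD of regucalcin, and if that is an SD of levels, true power is above 15%. This stands as a qualification: the 15% belongs to an unadjusted comparison, or to 192.4 being the SD of change. It does not rescue 0.65, which needs a correlation of about 0.87 or more even when three visits are averaged, and section 2.3 states none.

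A four-visit interaction with f = 0.1 gives 60% to 70% power at N = 90 for correlations of 0.5 to 0.6, and the figure may have arisen that way. But f = 0.1 is a much larger effect than 38.48 AU, which is f of about 0.04, and with 72 evaluable it gives only 49% to 59%.

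A second objection is that the power may not be the faulty entry. At 45 per arm, 0.50 SD gives almost exactly 0.65, so the stated difference or SD could be wrong instead. This cannot be settled from the document, and the correction should therefore begin by finding the faulty input.

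Two smaller points also stand. The 13% applies only if the 20% loss comes out of the 90. And regucalcin is a secondary outcome in section 2.7.2, so the error does not show that the balance comparison is underpowered; it shows that N = 90 has no valid stated justification.

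**Conclusion.** The concern holds. With the stated difference, SD, alpha and group size, power is 15.5% with 45 per arm and 13.3% with 36, against a claimed 65%, so the claim is about four times too high. This assumes a two-sided, unadjusted comparison; one-sided testing gives 24% and 21%. With an assumed correlation of 0.5 to 0.8, a baseline-adjusted month-6 comparison has 16% to 35% and the planned group × time test 10% to 30%. Every route to 0.65 needs either a high correlation that the protocol does not state or a difference about 2.5 times the stated one. It must be corrected because these are published figures that contradict each other, not a detail left to another document.

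**What to change.** Keep N = 90 and correct section 2.3.

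1. Go back to the original calculation and establish whether the difference, the SD, the power or the method was misreported. If a within-person correlation was used, state it with its source and recompute. Say whether 192.4 is the SD of levels or of change.
2. If the stated inputs stand, replace the power claim with wording such as:

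> With 45 participants per arm and a two-sided alpha of 0.05, power for a difference of 38.48 AU with an SD of 192.4 is about 15% without baseline adjustment (about 13% with 36 evaluable per arm after 20% loss). The difference detectable with 65% power is about 96 AU (108 AU with 36 per arm), and with 80% power about 115 AU (129 AU).

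3. State the sidedness of alpha and whether 90 is the number before or after allowing for the 20% loss.

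Reporting regucalcin as an estimate with its confidence interval, labelled exploratory, would suit this power; it is advisable but separate from the arithmetic correction.

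The cost is wording only. No participants are added, and the price is a less favourable power statement.
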